**Methods/design:**

This hybrid implementation/effectiveness implementation study is guided by organizational change theory as conceptualized in the Texas Christian University Program Change Model (PCM), a model of phased organizational change from exposure to adoption, implementation, and sustainability. The primary implementation aims are to assist 10 community-based organizations (CBOs) to implement and sustain Eban II; specifically, to partner with CBOs to expose providers to the intervention; facilitate its adoption, implementation and sustainment; and to evaluate processes and determinants of implementation, effectiveness, fidelity, and sustainment. The primary effectiveness aim is to evaluate the effect of Eban II on participant (n = 200 couples) outcomes, specifically incidents of protected sex and proportion of condom use. We will also determine the cost-effectiveness of implementation, as measured by implementation costs and potential cost savings. A mixed methods evaluation will examine implementation at the agency level; staff members from the CBOs will complete baseline measures of organizational context and climate, while key stakeholders will be interviewed periodically throughout implementation. Effectiveness of Eban II will be assessed using a randomized delayed enrollment (waitlist) control design to evaluate the impact of treatment on outcomes at posttest and three-month follow-up. Multi-level hierarchical modeling with a multi-level nested structure will be used to evaluate the effects of agency- and couples-level characteristics on couples-level outcomes (*e.g.*, condom use).

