### Primary effectiveness aim

#### Aim three

To evaluate the effect of intervention implementation on participant outcomes, specifically incidents of protected sex and proportion of condom use.

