### The Eban II intervention

This eight-week, standardized, manualized intervention is facilitated by a male–female team. The intervention (see Table 2) involves: strategies that address the broad array of factors influencing risk behavior among HIV-affected couples; dyadic and group processes that take advantage of relationship and group dynamics; and educational and culturally appropriate sessions [45].

**Table 2 T2:** Core elements of the Eban II intervention

**Sessions**	**Core elements**
**Sessions**	**Principles**
1. ‘Preparing for the Journey’ (Group Session)	Gender, Ethnic, and Cultural Pride
2. ‘Enhancing Couple Communication’ (Couple session)	The Talk and Listen Technique
	Triggers to Risky Behavior
	Learn to Problem Solve with ‘FENCE’
	Identifying Sexual Abuse
3. ‘Tools for the Journey’ (Couple session)	Condom Use
4. ‘Sharing the Load’ (Couple session)	Gender, Ethnic, and Cultural Pride as Couples
5. ‘It Takes a Village’ (Group session)	Reframing Difficult Situations
6. ‘Strengthening the Village’ (Group session)	Self Talk and Relapse Prevention
7. ‘Expanding the Village’ (Group session)	Networking with others and sexual communication with partners
8. ‘Celebrating our Relationship’ (Couple session)	A review of Nguzo Saba principles of unity and rededication to protecting each other

Unlike a traditional RCT, individuals in this study will not be incentivized for attending sessions. However, our experience indicates that incentives enhance attendance and active participation; community agencies frequently provide such incentives to enhance participation in routine programs. Therefore, we will provide minimal participation incentives similar to those often provided routinely by the agencies, such as bus tokens and gift cards at pre-, post-, and three-month follow-up. In addition, usual care, services, and referrals will be available to the WL couples while they wait to enter the risk reduction program. We will learn more about the impact of incentives during sustainability, when these incentives are no longer provided.

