### Measures to be completed by clients

Primary behavioral and physiologic outcomes are as follows:

1. Percentage of condom-protected sexual acts in the past 90 days.

2. Number of episodes of unprotected sexual intercourse.

3. Number of sexual partners.

4. Types of partners (primary, casual, new).

5. Frequency of oral, anal, and vaginal sex.

6. Use of alcohol and other drugs prior to sexual intercourse.

7. Partners’ risk status (*e.g.*, sexual partner has other partners).

We will also track concurrency, seroconversion, and incident STIs. In order to control for response bias, several steps will be taken, including: assessing sexual behaviors over a relatively brief period (*i.e.*, past three months at baseline and follow-ups and past seven weeks at post-intervention); providing participants with a calendar for benchmarking salient dates; involving only trained data collectors in the data collection; using the ACASI; and administering a five-item measure of social desirability bias [54].

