### Sample size calculation and power analyses

Sample size calculation and power analyses were conducted at both the agency- and couple-levels to ensure that we have sufficient statistical power for all analyses. At the agency level, the power analysis was based on the comparisons of key measures from providers (*e.g.*, provider attitudes toward evidence-based practices). From the 10 selected agencies, we will collect data from 100 non-clerical staff (10 providers per agency) in order to provide sufficient power to examine the within- and between-agency variation. With a type I of 0.05, type II error of 0.2 (or power of 80%), intra-agency correlation at 0.15 level, 100 raters from the 10 agencies will enable us to detect an effect size as small as 0.9 in standard deviation unit for measures from staff [65,66]. Non-parametric and parsimonious models will be used to accommodate the limitation of a relatively small number of agencies.

At the couples level, calculations were carried out based on the comparison of key outcome measures of incidents of unprotected sex and an increase in the proportion of condom use (*i.e.*, the number of times condoms were used during intercourse divided by the number of times sexual intercourse is reported) between intervention and waitlist control. With a repeated measures design, type I error 0.05, type II error 0.20, intra-couple correlation 0.4, the mean number of available repeated measures 2.5 (from baseline, post and three-month measurements), and a 2:1 ratio of intervention and waitlist control, a total of 174 couples would allow us to detect an effect size as small as 0.30 in standard deviation unit for number of unprotected sexual intercourse acts [65,67]. Thus, our planned sample of 180 couples provides sufficient power.

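### The protocol article defines its primary outcomes in conflicting ways (seven listed, two in the aim, one sized), so the stated 0.05 is not tied to a defined effectiveness claim

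*Protocol article*

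**What the plan says.** All references are to the protocol article.

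- *Measures to be completed by clients* opens with "Primary behavioral and physiologic outcomes are as follows" and numbers seven items. The first two are the percentage of condom-protected acts and the number of unprotected episodes. The other five include "Types of partners (primary, casual, new") and the frequency of three kinds of sex. Seroconversion and incident STIs are mentioned after the list as things also tracked.
- *Aim three*, the primary effectiveness aim, names two outcomes: "specifically incidents of protected sex and proportion of condom use". The abstract does the same.
- *Sample size calculation and power analyses* says the couples-level calculation rests on "key outcome measures of incidents of unprotected sex and an increase in the proportion of condom use". Its assumptions begin "With a repeated measures design, type I error 0.05, type II error 0.20". The detectable effect, 0.30 SD with 174 couples, is given only "for number of unprotected sexual intercourse acts".
- The abstract says the design will "evaluate the impact of treatment on outcomes at posttest and three-month follow-up". *Specific aim three* of the data analysis plan puts baseline, posttest and three-month data into repeated-measures and multi-level models. It names no primary outcome and no primary contrast.

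**The concern.** A type I error of 0.05 means something only when the claim it protects is defined. Here three sections define the primary set differently, and none says what result would count as showing effectiveness. The headline outcome could therefore be chosen after the results are seen, from as many as seven measures, while the report still cites 0.05.

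The seven-item list also works badly as a primary set. Types of partners and frequency of oral, anal and vaginal sex have no stated direction of benefit, and the latter is three behaviours in one item. No item is physiologic, although the list's title says some are.

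Nor are protected and unprotected sex two names for one outcome. A couple who have less sex overall can cut unprotected acts without adding any protected ones.

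**Working it through.** **1. The sections side by side**

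| Section | Outcomes given as primary or key | Detectable effect |
|---|---|---|
| Measures to be completed by clients | 7 | none |
| Abstract; Aim three | 2 (protected sex; condom-use proportion) | none |
| Sample size calculation | 2 (unprotected sex; condom-use proportion) | 1 (unprotected acts) |

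**2. What the 0.05 was attached to.** Inputs from the sample size section: 0.30 SD, 80% power, 2:1 allocation, 2.5 measures per couple, correlation 0.4. Sidedness is not stated; two-sided is assumed.

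- Before any design factor, total couples = 3 × (1 + 1/2) × ((1.960 + 0.842)/0.30)² = 392.4.
- Repeated-measures factor (1 + 1.5 × 0.4)/2.5 = 0.64, giving 251.2.
- With an assumed two-partner factor (1 + 0.4)/2 = 0.70, the result is 175.8, so 176 against 174 stated.

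The figure is thus reproduced closely as one outcome and one contrast at 0.05, provided the two-partner factor is assumed.

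**3. False-positive chance if any primary outcome may carry the claim.** This assumes one two-sided test per outcome at 0.05 and no true effect. If independent, the chance is 1 − 0.95^k:

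- k = 1: 5%
- k = 2: 1 − 0.95² = 9.75%
- k = 7: 1 − 0.95⁷ = 30.2%

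With equally correlated normal test statistics (400,000 simulated draws; the correlations are assumptions):

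| Correlation | 2 outcomes | 7 outcomes |
|---|---|---|
| 0.3 | 9.5% | 27% |
| 0.5 | 9.0% | 23% |
| 0.7 | 8.4% | 18% |
| 0.9 | 7% | 11% |

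**4. What sharing the 0.05 would cost.** Take the article's own 80% power at 174 couples as the anchor. At 180 couples, power per test is Φ(2.802 × √(180/174) − z), where z is the two-sided critical value.

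- Two outcomes at 0.025 each (z = 2.241): about 73%.
- Seven outcomes at 0.0071 each (z = 2.690): about 56%.

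**5. Whether the three-month visit alone could serve.** With 118 and 62 couples (*Screening and enrollment of couples*), 0.30 SD and no attrition:

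- SE = √(1/118 + 1/62) = 0.157 SD, so power = Φ(0.30/0.157 − 1.96) ≈ 48%.
- With the assumed two-partner factor of 0.70: about 63%.
- With baseline adjustment at an assumed correlation of 0.4 as well (further factor 1 − 0.4² = 0.84): about 70%.

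All are below the planned 80%, because the article sized a repeated-measures effect and not a single visit.

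**The case against.** The strongest reply is that this is a journal article, that a multiplicity rule commonly sits in an analysis plan not shown here, and that the effectiveness claim is really the two outcomes of Aim three. Much of this stands. Silence on how 0.05 is shared is not a fault in itself. The inflation in step 3 is what the wording permits; it is not a declared plan. The seven-outcome figure also counts items with no direction of benefit and no stated hypothesis, so it is the high end. On the Aim three reading the figure is 9.75% at most. The reply does not remove the contradiction, because the primary label, the aim and the sized outcome all stand in this document and disagree.

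Two stronger readings are tempting and are not supported:

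- A reader might infer that every outcome is tested separately at posttest and at three months at 5%, making 14 tests and a 51% false-positive chance if independent (1 − 0.95¹⁴). The article names two visits but does not state separate tests. The repeated-measures models it describes can give one treatment effect per outcome. Separate tests by visit would raise the error, but that is an assumption.
- A reader might infer that success on any one of the seven establishes effectiveness. No such rule is written.

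It would also be inaccurate to say that the power calculation considers one outcome: it names two and sizes one.

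**Conclusion.** The primary outcome set is contradictory and should be reconciled. *Trial status* reports that data cleaning and analysis have not begun, so naming the primary outcome now is still credible.

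The stated 0.05 holds for the effectiveness claim only with one primary outcome and one contrast. Under an any-success reading with one test per outcome, the rate would be 30% for seven independent outcomes (about 23% at correlation 0.5, 18% at 0.7). For the two Aim three outcomes it would be 9.75%, or about 7% to 9% if correlated. These figures rest on assumed correlations and on a success rule that the article does not state. The contradiction itself rests on no assumption.

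**What to change.** - In *Measures to be completed by clients*, make the number of unprotected acts the single primary outcome. Test it once at 0.05 by the treatment effect from the repeated-measures model over posttest and three months, in keeping with the design that the sample size section sized.
- Test condom-use proportion second in a fixed sequence, only if the first test succeeds. This keeps the overall error at 0.05 and takes no power from the first test.
- Relabel items 3 to 7 as secondary or descriptive, and delete physiologic from the list's title.
- In the abstract and Aim three, change protected to unprotected sex, to agree with the outcome list and the sample size section.

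If the sponsor prefers a three-month-only contrast, its power must be restated (step 5). Two primary outcomes with the 0.05 shared would also cure the contradiction, at the lower power in step 4. In either case the sample size section should say what the correlation of 0.4 refers to: with the repeated-measures factor alone, the stated inputs give 252 couples, not 174.

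The main change needs no new data. Its cost is that items 3 to 7 lose primary status.

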### Data management and analysis procedures

#### Quality control procedures

Quality control procedures include quality controls during the training of the co-facilitator teams; and during the running of groups, including checks of a random sample of audiotaped sessions and providing supervision and corrective feedback as needed. Co-facilitator teams will be asked to complete process notes at the end of each session, and couples will complete satisfaction ratings at the end of each session. Co-facilitator teams, site coordinators, and couples will also be asked to provide an overall evaluation of perceived effectiveness and their level of overall satisfaction with the intervention at the posttest assessment session.

### Sample size calculation and power analyses

Sample size calculation and power analyses were conducted at both the agency- and couple-levels to ensure that we have sufficient statistical power for all analyses. At the agency level, the power analysis was based on the comparisons of key measures from providers (*e.g.*, provider attitudes toward evidence-based practices). From the 10 selected agencies, we will collect data from 100 non-clerical staff (10 providers per agency) in order to provide sufficient power to examine the within- and between-agency variation. With a type I of 0.05, type II error of 0.2 (or power of 80%), intra-agency correlation at 0.15 level, 100 raters from the 10 agencies will enable us to detect an effect size as small as 0.9 in standard deviation unit for measures from staff [65,66]. Non-parametric and parsimonious models will be used to accommodate the limitation of a relatively small number of agencies.

At the couples level, calculations were carried out based on the comparison of key outcome measures of incidents of unprotected sex and an increase in the proportion of condom use (*i.e.*, the number of times condoms were used during intercourse divided by the number of times sexual intercourse is reported) between intervention and waitlist control. With a repeated measures design, type I error 0.05, type II error 0.20, intra-couple correlation 0.4, the mean number of available repeated measures 2.5 (from baseline, post and three-month measurements), and a 2:1 ratio of intervention and waitlist control, a total of 174 couples would allow us to detect an effect size as small as 0.30 in standard deviation unit for number of unprotected sexual intercourse acts [65,67]. Thus, our planned sample of 180 couples provides sufficient power.

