Data regarding acceptability, barriers, and facilitators will be derived from interviews and implementation-focused evaluation measures. As we are examining implementation in 10 large, diverse CBOs, barriers and facilitators will likely vary by agency. The qualitative data will provide the research team with extensive information about acceptability, barriers, and facilitators. In addition, we will examine the facilitator and couples’ satisfaction ratings to characterize acceptability of the intervention. These ratings will be compared both within and across agencies. Potential determinants of adoption and fidelity include but are not limited to training factors, competency at delivering the intervention, types of facilitators (*e.g.*, whether agencies used their own staff as facilitators or used the floating facilitator team), couple ‘mix’ in a given cohort, retention, and satisfaction. All of these factors will be examined when characterizing fidelity across agencies. In addition, based on interviews with facilitators and clients, we will remain open to other determinants that may emerge during implementation. There are several possible determinants of sustainability. We hypothesize that sustainability will be achieved in agencies that have their own trained staff facilitators who deliver the intervention with fidelity and who had positive experiences with the intervention during the implementation phase. To test this hypothesis, we will perform analyses in two levels: (1) Bivariate analyses between sustainability and characteristics of the CBOs and staff. The Pearson Chi-square will be used to test association. ANOVA will be used to test the means of the continuous measures (*e.g.*, ‘the number of agencies that continue to implement Eban II with fidelity’) across the different levels of a categorical measure (‘Does your agency have specific services for high-risk or HIV-positive couples? Yes/no’) at each time point of data collection; (2) Longitudinal analyses for long-term effects. Generalized linear mixed models (GLMM) [67,68] will be used to evaluate the relationship between sustainability and characteristics of the CBOs. GLMM cannot only model global fixed effects (*e.g.*, the number of full-time staff), but also can model random variation (*e.g.*, change over time of individual agency), which is particularly useful.

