### Specific aim three

We will use repeated measures regression models and multi-level hierarchical modeling [70,71] to evaluate the effect of characteristics of agencies, staff, and couples on the behavioral and psychosocial outcomes. For repeated measures regression models, we will directly incorporate measures into models and deal with intra-class correlations from agency and staff through covariance matrix. With the multi-level nested structure from individuals, couples, agencies, and staff, the hierarchical models will be fitted in three possible steps: (a) to set the foundation for a class of hierarchical models, first we will construct individual-couple-level models with repeated measurements (baseline, post and three-month) within a couple that involves time (and intercept); (b) we will then construct across the couples-level models that involve explanatory variables such as couple demographics; health history; history of alcohol and recreational drug use; HIV/AIDS risk reduction knowledge; perceived couple sexual norms; intervention components, and a binary variable indicating immediate active treatment or wait list control; (c) we will model the regression coefficients obtained from step b at the agency level as functions of explanatory variables of agency characteristics (*e.g.*, organization size and budget, number of staff, etc.). Finally, we will then combine models from steps a, b, and c to form the complete model, which will be estimated through special procedures and software, such as WinBUGS and MlwiN [72,73].

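### The plan claims enough power for every analysis, but it calculates power for only two comparisons; the sustainability test and the agency-level moderators rest on 10 agencies and have no calculation.

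*Protocol article*

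**What the plan says.** The section on sample size and power opens by saying that calculations were made at agency and couple level "to ensure that we have sufficient statistical power for all analyses". Two follow.

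- **Agency level:** "the power analysis was based on the comparisons of key measures from providers". With type I error 0.05, power 80% and intra-agency correlation 0.15, "100 raters from the 10 agencies will enable us to detect an effect size as small as 0.9 in standard deviation unit". The section then acknowledges that there are few agencies and answers with non-parametric and parsimonious models.
- **Couple level:** 174 couples, 2:1, to detect 0.30 SD between intervention and waitlist.

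Two planned analyses have the agency as the independent unit.

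- **Specific aim two:** "We hypothesize that sustainability will be achieved in agencies that have their own trained staff facilitators who deliver the intervention with fidelity" (and had positive experiences with it). To test this, "The Pearson Chi-square will be used to test association", with ANOVA for continuous measures and then mixed models over time. The Sustainability section makes sustainability a status that each agency either achieves or does not.
- **Specific aim three, step (c):** "we will model the regression coefficients obtained from step b at the agency level as functions of explanatory variables of agency characteristics", with size, budget and staff number as examples. Steps (a) to (c) are then combined into one model.

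**The concern.** The opening claim covers every analysis, but neither calculation bears on a comparison between agencies. Recruiting more staff raters or more couples does not add agencies, so both analyses above have 10 independent units however many people are measured.

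What determines sustainability is part of a primary implementation aim, and the plan states a directional hypothesis for it with a named test. If a test on 10 agencies often misses even a strong determinant, a blanket assurance of adequate power invites a reader to take a non-significant result as showing that trained staff facilitators, fidelity or agency characteristics do not matter.

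**Working it through.** **1. The plan's own agency-level figure.** Inputs from the sample size section: 10 raters in each of 10 agencies, correlation 0.15, 0.05, 80%. Two-sided testing is assumed. Design effect = 1 + (10 − 1) × 0.15 = 2.35. For two groups of 5 agencies (50 raters each), the detectable difference is (1.960 + 0.842) × √(2.35 × (1/50 + 1/50)) = 0.86 SD; a 6:4 split gives 0.88. Both round to the stated 0.9, so the figure reproduces. It applies to staff ratings only.

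**2. Sustainability, 10 agencies, 2x2 table.** The documents give no expected rates, so those below are assumptions. Agencies are taken as independent. Power is the summed binomial probability of all tables that reject (Pearson: chi-square > 3.841; Fisher: p < 0.05).

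By hand for 5:5 and 80% v 20%: Fisher rejects at 5 v 0, 5 v 1 and 4 v 0 sustained. The group probabilities are 0.8⁵ = 0.328 for 5 of 5 (or 0 of 5 in the other group) and 0.410 for 4 of 5 (or 1 of 5). The sum is 0.328² + 2 × 0.328 × 0.410 = 0.107 + 0.268 = 0.376. Pearson also rejects at 5 v 2 and 3 v 0, adding 2 × 0.328 × 0.205 = 0.134, for 0.510. Mirror-image tables add almost nothing.

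| Sustained | Test | 5:5 | 6:4 | 7:3 | 8:2 |
|---|---|---|---|---|---|
| 80% v 20% | Pearson | 51% | 48% | 52% | 38% |
| | Fisher | 38% | 38% | 30% | 11% |
| 80% v 40% | Pearson | 27% | 21% | 28% | 26% |
| | Fisher | 14% | 18% | 13% | 6% |
| 90% v 10% | Pearson | 82% | 80% | 83% | 74% |
| | Fisher | 74% | 74% | 62% | 35% |

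The 80% v 40% rows give the larger group the higher rate. Reversed, power at 8:2 falls to 7% (Pearson) and 1% (Fisher).

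**3. Validity of the Pearson test here.** The four expected counts sum to 10, so they average 2.5 and cannot all exceed 5. By enumeration over null rates from 5% to 95%, the real size at nominal 5% reaches about 6% at 5:5 and about 9% at 8:2.

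**4. Step (c).** At least 18 couples per agency at 2:1 is 12 v 6. If V is the variance of a couple's summary outcome in SD² units, the SE of one agency's arm effect is √(V × (1/12 + 1/6)). The SE of a slope per SD of an agency characteristic is that divided by √9. Two values of V:

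- V = 0.64, from the stated correlation 0.4 and 2.5 measures: (1 + 1.5 × 0.4)/2.5. SE 0.40, slope SE 0.133.
- V = 0.44, implied by 174 couples: (0.30/2.802)² / (1/116 + 1/58). SE 0.33, slope SE 0.111.

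Power for a change in the arm effect per SD of a characteristic:

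| Change | V | t, 6 df (three characteristics) | t, 8 df (one) | Normal reference |
|---|---|---|---|---|
| 0.30 SD | 0.64 | 47% | 51% | 61% |
| 0.30 SD | 0.44 | 62% | 66% | 77% |
| 0.15 SD | 0.64 | 16% | 17% | 20% |
| 0.15 SD | 0.44 | 21% | 22% | 27% |

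All of these assume no residual variation of the arm effect between agencies. Any such variation lowers them.

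**The case against.** **The limitation is disclosed.** The sample size section says the agencies are few, Specific aim two repeats it, and the agency-level calculation is introduced as one for provider measures. That is fair, but parsimonious or non-parametric models do not create power, and the acknowledgement does not withdraw the claim about all analyses made in the same paragraph.

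**The 2x2 test is only one analysis.** Sustainability is also described by couples recruited, enrolled and completing and by technical assistance, with ANOVA and longitudinal mixed models. This is correct. The independent units are still 10.

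**The effects are the reviewer's choice.** This stands. A reader might infer that power is about half or less for any very large effect. The documents do not support that: 90% v 10% gives 74-83% by Pearson, and in step (c) a change of 0.45 SD reaches 80% even with V = 0.64 and 6 df.

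**Step (c) may not be a ten-point regression.** A reader might also take the 47% as the power of step (c). It rests on a variance that does not match the 174 couples, on three characteristics entered together (the protocol lists them only as examples), and on a two-stage fit although a combined model is planned. Only the range is defensible. Step (c) also models other coefficients besides the arm effect.

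**Nothing is miscalculated, and no misreading is planned.** Both true. The 0.9 SD reproduces, and the protocol nowhere says it will read non-significance as no association. Exploratory labelling and choice of exact test could sit in an analysis plan. The claim of power for all analyses, however, is made in this document.

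**Conclusion.** The concern holds as a matter of scope: the power statement covers more than its two calculations support. For the sustainability hypothesis, a 60-point difference between groups of agencies has 38-52% power by the named test and 11-38% by Fisher's, and a 40-point difference at most about 28%. Only near-complete separation approaches 80%. These figures assume two-sided 0.05, independent agencies and rates that the documents do not give.

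For step (c) there is no power calculation and no single figure can be defended: about 47-77% for a 0.30 SD change in the arm effect per SD of a characteristic and 16-27% for 0.15 SD, before any residual between-agency variation. Even the more favourable set, for a moderation as large as the whole effect the trial is sized for, stays below 80%.

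The staff-measure figure and the couples' arm contrast are untouched by this point.

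**What to change.** - In the sample size section, limit the power claim to staff measures and the couples' arm contrast.
- State that analyses with the agency as unit (determinants of sustainability and step (c)) have 10 units, are exploratory, are reported as estimates with intervals, and that a non-significant result is not evidence of no association.
- In Specific aim two, replace the Pearson chi-square with an exact test for 2x2 tables of 10 agencies.
- Optionally, enter agency characteristics in step (c) one at a time, chosen in advance.

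The cost is a narrower power claim and a somewhat conservative test: at 5:5 and 80% v 20%, Fisher's test has 38% power against 51% for Pearson. The article reports that data analysis had not begun, so these changes could still be made in advance of it.
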